### Primary outcomes and measures

The primary outcome is reported improvements in the safety and wellbeing of women and children affected by the behaviour of KODY participants. Primary and secondary outcomes, and proposed measures, are outlined in Table 1. The measures will be tested for feasibility during the program pilot and then implemented with necessary adjustments during the trial proper. Measures have been selected in consultation with program staff to ensure their suitability for program outcomes. Where appropriate, brief versions of measures were selected to reduce participant burden, as well as measures that were already used for assessment by program staff. A range of validated and unvalidated measures were selected as validated measures identified in the literature alone were not seen to adequately measure outcomes.

#### Composite abuse scale

The primary outcome of improved safety and wellbeing of women is measured by the Composite Abuse Scale Standard Form [33], a 30-item self-report measure completed by the mothers involved in the KODY evaluation to identify the nature and severity of their (ex)partner’s abusive behaviour. Statements describing partner behaviours are scored on a 6-point scale (‘never’ to ‘daily’) to assess the frequency of these behaviours across time. Statements reflect four categories of abuse: severe combined abuse, emotional abuse, physical abuse and harassment. A reduction in scores represents a decrease in women’s experiences of these (ex)partner behaviours.

Several measures are used to assess the primary outcome of improved safety and wellbeing of children. These include the Emotional Dysregulation Scale, the Interpersonal Mindfulness in Parenting scale, the Brief Infant–Toddler Social and Emotional Assessment and the Strengths and Difficulties Questionnaire, as outlined below.

#### Emotional dysregulation scale

The Emotional Dysregulation Scale [34] is a 12-item validated measure used to determine overall individual emotional dysregulation. This scale was selected considering research showing that children are less safe when their fathers’ emotions are dysregulated [35], particularly in the context of substance use [36], as well as in recognition of *Caring Dads*’ focus on explicitly teaching skills related to emotion regulation. In the KODY evaluation, fathers answer questions about their own emotion regulation abilities, while mothers are asked to report on their (ex)partner’s emotion regulation abilities. Items are scored on a 7-point scale (‘not true’ to ‘very true’). Items assess domains of emotional experiencing, cognition and behaviour.

#### Interpersonal mindfulness in parenting scale

The Interpersonal Mindfulness in Parenting Scale [37] is a 27-item self-report scale that measures mindfulness in the parenting context. This scale aligns with ‘child-centred fathering’, a concept central to the *Caring Dads* program, with items suitable for assessing fathers’ skill improvement, as well as their ability to regulate their emotions when parenting, complementing findings from the Emotional Dysregulation Scale. Items are scored on a 5-point scale (‘never true’ to ‘always true’). Items assess mindful parenting across five dimensions: listening with full attention, non-judgmental acceptance of self and child, compassion for self, emotional awareness of self and child, and self-regulation in parenting.

#### Strengths and difficulties questionnaire

The Strengths and Difficulties Questionnaire [38] is a 25-item validated measure that assesses child mental health in children aged 3–16 years. In the KODY evaluation, this questionnaire will be completed by mothers to measure improvements in children’s mental health and wellbeing over time. Mothers use a 3-point scale (‘not true’ to ‘certainly true’) to indicate how well a range of statements describe their child. These statements describe child behaviours across five domains: emotional problems, conduct problems, hyperactivity, peer relationship problems, and prosocial behaviour. This scale was selected for the KODY evaluation to complement the Brief Infant–Toddler Social and Emotional Assessment by assessing child wellbeing across an older age group. Adolescents involved with KODY will also be invited to complete this measure.

#### Brief infant–toddler social and emotional assessment

The Brief Infant–Toddler Social and Emotional Assessment [39] is a 42-item parent-report validated measure used to screen for social-emotional and behavioural problems and developmental delay in children aged 1–3 years. In the KODY evaluation, mothers will use a 3-point scale (‘not true/rarely’ to ‘very true/often’) to indicate how well a range of statements describe their child’s behaviour. These statements describe child behaviours across two subscales: the problem scale, measuring behaviours that, if present, represent a problem; and the competence scale, measuring behaviours that, if absent, represent a problem. This scale complements the Strengths and Difficulties Questionnaire by assessing child wellbeing in a younger age group.

### Secondary outcomes and measures

The secondary outcome of fathers’ use of DV relates directly to the primary outcomes of improved safety and wellbeing for women and children, as DV is seen as a major risk. Further, the secondary outcome of fathers’ use of AOD, will also contribute to the primary outcomes, given the evidence that where fathers use both DV and AOD, the severity of abuse, and therefore the risk to safety is significantly higher [1]. The secondary outcome of fathers’ use of DV will be assessed through reporting from fathers and mothers, using an adapted Mirabal measure, the Anger Management Scale, and the Brief Irritability Test.

#### Adapted mirabal measure

For the KODY evaluation, the research team has created an 18-item measure, adapted from an existing measure used in Project Mirabal, a multi-site longitudinal study of domestic violence perpetrator programs, conducted between 2009 and 2015 in the UK [40]. The adapted measure has a version for mothers and one for fathers, in order to assess and compare mothers’ and fathers’ perceptions of fathers’ behaviour change over time. Mothers and fathers respond to a range of statements on a 4-point scale (‘strongly disagree’ to ‘strongly agree’).

The adapted Mirabal uses items from four of the six indicators of change outlined in Project Mirabal, asking mothers to assess their (ex)partner’s respectful communication, fathering, awareness of self and others, and their own perceptions of their children’s experiences (e.g. ‘My children worry about the safety of their mother’). Fathers who have used violence are provided with a similar range of statements, across the same domains.

#### Anger management scale

The Anger Management scale is a 12-item subscale of the Personal Relationships Profile, a validated measure developed by Straus and colleagues [41]. This scale asks fathers to assess their ability to recognise and control their anger towards the mother of their children. It was used with fathers in the Victorian *Caring Dads* trial [3], and found an overall increase in men’s scores from baseline to post-program time points, indicating an improvement in men’s ability to recognise and control their anger after completing the *Caring Dads* program. Items are scored on a 4-point scale (‘strongly disagree’ to ‘strongly agree’) and includes items from three subscales: behavioural self-soothing, recognising signs of anger and self-talk.

#### Brief irritability test

The Brief Irritability Test [42] is a 5-item scale that measures the degree to which respondents experience frustration and irritability. This scale was selected for use with fathers in the KODY evaluation to complement the Anger Management scale. Irritability is similar to anger, but often persists for longer and is outwardly expressed in the form of aggressive behaviour [42]. As high levels of irritability are also associated with higher levels of stress, this measure was selected to provide some insight into fathers’ wellbeing. Items are scored on a 6-point scale (‘never’ to ‘always’) to indicate how frequently respondents identify with each statement, considering their feelings over the past two weeks. The secondary outcome of fathers’ use of AOD will be assessed through reporting from fathers, using the Alcohol Use Disorders Identification Test and the Drug Use Disorders Identification Test.

### Alcohol use disorders identification test and drug use disorders identification test

The Alcohol Use Disorders Identification Test (AUDIT) [43] is a 10-item self-report screening tool developed by the World Health Organization to assess alcohol consumption, drinking behaviours and alcohol-related problems. The Drug Use Disorders Identification Test (DUDIT) [44] is an 11-item self-report screening tool, developed as a parallel instrument to the AUDIT, to assess use of drugs other than alcohol and drug-related problems. Both the AUDIT and the DUDIT have been validated across genders and in a wide range of culturally and linguistically diverse groups. These tools were selected to provide insight into fathers’ AOD use.

### Data collection

The outcomes evaluation will involve data collection at four timepoints (see Table 2). Psychometric tests will be administered to men and women participants at three timepoints—baseline (T1), post-*Caring Dads* program (T2) and three months after the end of the *Caring Dads* program (T3) (see Table 2). Men and women will receive a small honorarium at each point of data collection to recognise the donation of their time.

**Table 2 Tab2:** Data Collection Timeline

Data Collection		Fathers	Mothers
Baseline	T1	▪Measures	▪Measures
post-*Caring Dads* program	T2	▪Measures ▪File Review ▪Process evaluation	▪Measures ▪File Review ▪Process evaluation
3-month follow up	T3	▪Measures ▪File Review ▪Process evaluation	▪Measures ▪File Review ▪Process evaluation
9-month follow up	T4	▪File Review to identify subsequent abuse concerns	▪File Review to identify subsequent abuse concerns

File reviews of KODY participants will be undertaken at T2, T3 and at 9-month follow up (T4) to obtain demographic data about participants, as well as program data, such as ‘dose’ level of expanded service, referral sources, other services involved with clients and accountability arrangements (e.g. court orders).

### Data management

Program participants and professionals will be assigned a unique research ID to ensure anonymity. Outcome measures will be completed online and stored in a secure Qualtrics database. Other research data will be stored in the University of Melbourne OneDrive system with access restricted to members of the research team. Interviews and focus groups will be audio-recorded with participant consent. If these are conducted online, recording will be through Zoom and saved directly into OneDrive. Recordings of face-to-face interviews and focus groups will also be uploaded onto OneDrive. Password protection on files will be used as required.

### Data analysis

Intent to treat analyses will be used so that all service users are included in the primary analysis, allowing for variations in levels of participation in KODY and including those who drop out prematurely. Assuming differences between groups, supplementary analyses will examine the extent to which intervention effects vary according to whether families received a higher or lower ‘dose’ of expanded service. Recognizing that fathers are not being randomly assigned to the intervention and comparison group, care will be taken to compare time 1 characteristics of groups and, if necessary, use propensity analyses in post-group and follow-up comparisons. Each component of the study will be analysed separately in the first instance, then brought together to triangulate data collection and analysis, before a final synthesis.

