### Recruitment and sampling

Recruitment into KODY and into ‘*Caring Dads* standard’ program will occur through referrals from a range of services, including other programs within Kids First and Odyssey House Victoria and external services such as the statutory child protection service, and other Melbourne-based DV and AOD services.

Fathers entering KODY or ‘*Caring Dads* standard’ programs will be assessed and invited at intake by program staff to participate in the evaluation, as will men’s (ex)partners. Researchers will follow up with interested participants to obtain informed consent which will be confirmed at each stage of data collection. Program staff will be consulted regarding any possible safety issues.

Three KODY groups and three ‘*Caring Dads* standard’ groups are planned for each year of the study, each with up to 10 participants. Assuming a medium effect size (based on Cohen’s d), a power of 0.80 and a two-tailed test across independent groups, this study will need to involve reports from 128 mothers, 64 in each of the KODY and comparison groups. Reported participation rates for evaluations of *Caring Dads* programs range from 62% [3] to 97% [5]. Assuming a partner contact success rate of 75% based on the benefits of the *Kids in Focus* program for women and children, this study will need to enrol 170 families across groups.

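### Adjustment for confounding is left to an undefined look at the baseline data, although the entry criteria already make the arms differ on a prognostic factor

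*Protocol article*

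**What the plan says.** The Data analysis section of the protocol article acknowledges that fathers are not randomly assigned and then states that "care will be taken to compare time 1 characteristics of groups and, if necessary, use propensity analyses in post-group and follow-up comparisons". It sets no threshold for when adjustment becomes necessary and names no covariates.

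Eligibility criteria defines the arms differently. KODY fathers are referred for problematic alcohol or drug use, are identified by AOD case managers as using or at risk of using domestic violence, and must be supported by Odyssey House clinicians. Comparison fathers need only have been identified as using, or at risk of using, domestic violence. Background describes substance use as one of few consistent predictors of continued violence, and reports that about a third of an earlier Caring Dads cohort were using AOD services. Secondary outcomes and measures adds that abuse is more severe where both problems are present.

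Recruitment and sampling sizes the study with "Assuming a medium effect size", "a power of 0.80 and a two-tailed test across independent groups", giving "128 mothers, 64 in each of the KODY and comparison groups". The outcome measures are taken at T1, T2 and T3 (Data collection).

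Primary outcomes and measures says: "The primary outcome is reported improvements in the safety and wellbeing of women and children affected by the behaviour of KODY participants". That sentence names no comparator, whereas the Abstract (Methods/Design) and the Discussion both define the primary outcomes by comparison with Caring Dads standard.

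**The concern.** In a non-randomised comparison, the case for adjustment comes from how the groups were formed, not from what a baseline table happens to show. Here the protocol supplies that case itself: the factor that separates the arms is one it calls prognostic for the primary outcome. Making adjustment optional has two consequences.

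- The form of the main comparison depends on the data and on judgement, because nothing defines when adjustment is needed.
- A moderate imbalance in abuse severity, or in another confounder, can be looked at, judged small and left in the effect estimate.

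This is more than detail left to a statistical analysis plan. The protocol states a rule, and a later plan that always adjusted would have to depart from it.

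**Working it through.** **Inputs from the protocol (Recruitment and sampling).** Medium effect by Cohen's d, power 0.80, two-tailed test on independent groups, 64 mothers per group, partner contact 75%, 170 families.

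**Assumptions, not in the protocol.** d = 0.5 for a medium effect; two-sided alpha 0.05; correlation r between the T1 and follow-up score of 0.5-0.6 for bias and 0.3-0.7 for precision; a true T1 imbalance of 0.2-0.5 SD; a p<0.05 t-test as the trigger for adjustment. The last is only a convenient stand-in, since the protocol does not say how necessity is judged.

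**1. The plan's own figure.** A two-sample t-test with d = 0.5, alpha 0.05 and power 0.80 needs 63.77 per group, so 64 and 128 in total (power 0.801). Enrolment is 128/0.75 = 170.67, against the stated 170. Both reproduce, which supports the assumed d and alpha.

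**2. How often a T1 test flags an imbalance.** Power of the same t-test at 64 v 64:

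| True T1 imbalance (SD) | Probability flagged |
|---|---|
| 0.2 | 0.20 |
| 0.3 | 0.39 |
| 0.4 | 0.61 |
| 0.5 | 0.80 |
| 0.8 | 0.99 |

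For substance use itself, with one third v an assumed 95% of fathers using AOD services, the probability is above 0.999.

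**3. Bias if adjustment is never made.** Bias = r x imbalance. For 0.3 SD: 0.5 x 0.3 = 0.15 SD and 0.6 x 0.3 = 0.18 SD, or 30% and 36% of d = 0.5. With bias 0.15 SD and no true effect, the type I error of the unadjusted test is 0.13.

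**4. Bias when the imbalance is missed.** Data sets that pass the check are those with a smaller observed imbalance, so the figures in step 3 overstate this case. Simulation (64 v 64, true imbalance 0.3 SD, 40,000 runs) gives a mean observed imbalance of 0.19 SD when the T1 test is not significant. Bias is then r x 0.19: about 0.09 SD at r = 0.5 and 0.11 SD at r = 0.6. Divided by 0.5, that is 19% to 23% of the planned effect.

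**5. The conditional procedure as a whole.** Adjusting by ANCOVA only when the T1 test on that score has p<0.05 (20,000 runs; true imbalances 0.2-0.5 SD; r = 0.5 and 0.7) gives a mean bias of about 0.02-0.08 SD and a type I error of about 0.05-0.065.

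**6. Precision from always adjusting for the T1 score.** The residual SD becomes sqrt(1 - r^2). At r = 0.5 this is 0.866, so the standardised effect is 0.5/0.866 = 0.577. Power at 64 per group is 0.84 (r = 0.3), 0.90 (r = 0.5) and 0.98 (r = 0.7), against 0.80 unadjusted. These are upper bounds: correlation between arm and covariate takes part of the gain back.

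**7. Overlap on substance use.** If only about a third of comparison fathers resemble KODY fathers (64/3, about 21), an unadjusted comparison of 64 v 21 at d = 0.5 has power of about 0.51.

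**The case against.** The strongest reply is that the protocol does plan to compare the groups at T1 and does name a suitable method. A visible imbalance would lead to adjustment, and the substance-use gap could hardly be overlooked. Step 5 supports part of this: under a strict significance trigger applied to the outcome's own T1 score, average bias is small and the type I error stays near nominal. But the protocol commits to no such trigger, and a discretionary one carries no such assurance. Nor does the comparison have to be a significance test. It might be made on standardised differences, in which case the flagging probabilities in step 2 would not apply as they stand.

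Three stronger readings are tempting, and the protocol does not support them.

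- A reader might infer that the baseline outcome is left out of the primary comparison. The article states no primary model. The wording "a two-tailed test across independent groups" shows how the sample size was set, not which covariates the analysis will use.
- A reader might infer that power is wasted. Sizing without a covariate is conservative, and the gain in step 6 rests on an assumed correlation.
- A reader might take the sentence in Primary outcomes and measures to mean a before-after analysis within KODY. The Abstract, Methods/Design and the Discussion all make the comparison between groups, so this is loose wording to be aligned.

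One caution about the remedy also stands. Referral source comes from file reviews described as being of KODY participants, from T2 onward, and co-residence is not listed as collected. Referral route also comes close to defining the arm. Neither should be made a compulsory covariate.

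**Conclusion.** The concern holds for the conditional rule itself. In a design whose entry criteria separate the arms on a factor that the protocol calls prognostic, adjustment is needed before any T1 data are seen and should not hang on an undefined judgement.

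The size is moderate. For a true 0.3 SD imbalance, a p<0.05 trigger would miss it about 61% of the time (1 - 0.39). The bias when missed is about a fifth of the planned effect, and about a third if adjustment is never made. These figures depend on the assumed imbalance, correlation and trigger, none of which the protocol gives. What does not depend on them is that the rule is stated without a criterion and that the arms differ by design.

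**What to change.** In Data analysis, delete the condition. State that the primary comparison between KODY and Caring Dads standard at T2 and T3 is always adjusted for the T1 score of the same measure and for T1 Composite Abuse Scale, AUDIT and DUDIT, whatever the T1 comparison shows. ANCOVA or a mixed model with propensity or overlap weighting would serve. Report standardised differences in place of baseline tests, together with an overlap check. Add further covariates only if they are collected at T1 in both arms and do not in effect define the arm. In Primary outcomes and measures, reword the primary outcome so that it is compared with Caring Dads standard, as in the Abstract and the Discussion.

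The cost is mainly wording, since the named scores are already planned at T1. The downside is that, if overlap on substance use is poor, the estimate may be less precise and apply to a narrower group of families. Weighting cannot repair that, but the overlap check would show it.

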## Discussion

This paper outlines the protocol for a quasi-experimental trial of the innovative KODY program, an all-of-family response to co-occurring issues of DV and AOD. A quasi-experimental design was deemed most appropriate for the trial, as randomized allocation to trial and comparison groups is impracticable and potentially unethical in the context of the program and the service system in which it operates. Primary outcomes for the study are the increased safety and wellbeing of mothers and children whose (ex)partners and fathers respectively participate in KODY (the trial program), when compared with ‘*Caring Dads* standard’ (the comparison group).

Through an analysis of both outcomes measures and file reviews to provide ‘dose’ level information, the study aims to build the evidence for program responses that increase the safety and wellbeing of women and children impacted by men who use DV and AOD. The innovative aspects of the program—addressing the co-occurrence of DV and AOD with a specific focus on fathering, providing support to all members of the family and centring the needs of children—are all drawn from both academic evidence and practitioner expertise. The innovative nature of the program may result in small sample sizes in the early years of implementation, which may limit the power of analyses, but the authors’ experience with the evaluation of other innovative programs suggests that sample sizes will increase with program longevity. Operating within the DV and AOD service sectors respectively, the two partner organisations—Kids First and Odyssey House Victoria—have a shared focus on the needs of vulnerable children and train their staff in a common framework (Safe and Together) which brings a shared language and conceptualisation of the intersection of AOD and DV [30]. In the study context of Victoria, Australia, their joint commitment to collaborating across these sectors exemplifies a shift in the service system context and policy drivers away from a siloed service system which results in separate and disconnected service responses, particularly when children are involved [21].

